**ASSESSMENT AT FOLLOW UP**

1. **Symptoms at follow up**

Heaviness *(Gaurava)* Weakness *(Daurbalya)* Fatigue *(Klama)*

0

0

Vertigo *(Bhrama)* Sleepiness (*Nidradhikya*) Bodyache*(Angamarda)*

0

0

Indigestion *(Avipaka)* Tastelessness *(Aruchi)* Anorexia *(Anannaabhilaashaa)*

0

0

Loss of appetite *(Agnimaandya)* Headache *(Shirahshoola)* Anosmia *(Gandha)*

0

0

Cough *(Kasa)* Rhinorrhea *(Pratishyaya)* Fever *(Jvara)*

0

0

Breathlessness *(Shvasa)* Headache *(Shirahshool)* Fever with chills ShitapurvakJvara)

0

0

Sore throat *(Gala Sanrambha)* Dysgeusia *(Aasyavairasya)*

0

Alertness Energetic Cheerful Calm

0

0

Depression Anxiety Forgetfulness Lack of enthusiasm

0

0

Insomnia Early awakening Lightness in head Drowsiness

0

0

Increased appetite Pain in abdomen Hyperacidity Nausea

0

0

Diarrhea Dysentery Constipation Vomiting

0

0

0

Excess salivation Dryness of mouth Mouth ulcers Stomatitis

0

0

Joint pains Muscle pains General stiffness Backache

0

0

Tremors Skin rash Itching Sweating

0

0

1. **Clinical assessment**

1. How many times do you eat every day? --------- times
2. Do you exercise regularly? Yes No ……… times in last week
3. Do you feel sensation of hunger? Yes No Unable to answer
4. How was your sleep yesterday? Sound sleep Disturbed sleep Unable to answer
5. Is your tongue quoted? Yes No Unable to answer
6. Please describe your bowel movements: Constipation Regular Irregular
7. How is your urine? Yellow Pale-Yellow Colorless Burning

1. **Ayurvedic Disease Subtypes / Stages**

Vyadhi: Vata Kaphaj Jvara / Other______________________________________­­­­­­_________

Vyadhi Sankara / Upadrava: _____________________________

Dosha Status: Vata Pitta Kapha Sannipatik / ­­___________

Avastha: Sama / Nirama

Dushya: Rasa Rakta Mamsa

Meda Asthi Majja Shukra

Adhishthan: Pranavaha Annavaha Rasavaha Raktavaha

Other_____­­­­­­­­­­­­­­­­­­­­­­­­­­­­­­­­­­­­____________________________________________________

1. **Vyadhibala:** Heena Madyama Uttam
2. **Rugnabala:** Heena Madyama Uttam
3. **Ancillary measures:**

Diet related: _______________________________________________________________

Behavioral changes: _________________________________________________________

## Appendix J: Daily Progress Report

**AYUSH COVID-19 PATIENT PROTOCOL 2020**

**DAILY PROGRESS REPORT:**

**Patient Number______________________ Patient Initials:__________________ Date of Admission______________________________**

| **SYMPTOMS** | **D1** | **D2** | **D3** | **D4** | **D5** | **D6** | **D7** | **D8** | **D9** | **D10** | **D11** | **D12** | **D13** | **D14** | **D15** | **D16** | **D17** | **D18** | **D19** | **D20** |
| --- | --- | --- | --- | --- | --- | --- | --- | --- | --- | --- | --- | --- | --- | --- | --- | --- | --- | --- | --- | --- |
| **FEVER** |  |  |  |  |  |  |  |  |  |  |  |  |  |  |  |  |  |  |  |  |
| **COUGH** |  |  |  |  |  |  |  |  |  |  |  |  |  |  |  |  |  |  |  |  |
| **SORE THROAT** |  |  |  |  |  |  |  |  |  |  |  |  |  |  |  |  |  |  |  |  |
| **DYSPNOEA** |  |  |  |  |  |  |  |  |  |  |  |  |  |  |  |  |  |  |  |  |
| **TASTE LOSS** |  |  |  |  |  |  |  |  |  |  |  |  |  |  |  |  |  |  |  |  |
| **SMELL LOSS** |  |  |  |  |  |  |  |  |  |  |  |  |  |  |  |  |  |  |  |  |
| **MYALGIA** |  |  |  |  |  |  |  |  |  |  |  |  |  |  |  |  |  |  |  |  |
| **CHILLS** |  |  |  |  |  |  |  |  |  |  |  |  |  |  |  |  |  |  |  |  |
| **NAUSEA** |  |  |  |  |  |  |  |  |  |  |  |  |  |  |  |  |  |  |  |  |
| **VOMITING** |  |  |  |  |  |  |  |  |  |  |  |  |  |  |  |  |  |  |  |  |
| **DIARRHOEA** |  |  |  |  |  |  |  |  |  |  |  |  |  |  |  |  |  |  |  |  |
| **PNEUMONIA** |  |  |  |  |  |  |  |  |  |  |  |  |  |  |  |  |  |  |  |  |
|  |  |  |  |  |  |  |  |  |  |  |  |  |  |  |  |  |  |  |  |  |
|  |  |  |  |  |  |  |  |  |  |  |  |  |  |  |  |  |  |  |  |  |

**REMARKS:__________________________________________________________________________________________________________________________________________________________________________________________________________________________________________________**

**AYUSH COVID-19 PATIENT PROTOCOL 2020**

**Patient Number______________________ Patient Initials:__________________ Date of Admission______________________________**

| **VITALS** | **D1** | **D2** | **D3** | **D4** | **D5** | **D6** | **D7** | **D8** | **D9** | **D10** | **D11** | **D12** | **D13** | **D14** | **D15** | **D16** | **D17** | **D18** | **D19** | **D20** |
| --- | --- | --- | --- | --- | --- | --- | --- | --- | --- | --- | --- | --- | --- | --- | --- | --- | --- | --- | --- | --- |
| **PULSE** |  |  |  |  |  |  |  |  |  |  |  |  |  |  |  |  |  |  |  |  |
| **BP** |  |  |  |  |  |  |  |  |  |  |  |  |  |  |  |  |  |  |  |  |
| **RR** |  |  |  |  |  |  |  |  |  |  |  |  |  |  |  |  |  |  |  |  |
| **SPaO2 (OXI)** |  |  |  |  |  |  |  |  |  |  |  |  |  |  |  |  |  |  |  |  |
| **COMPLICATIONS** | | | | | | | | | | | | | | | | | | | | |
| **OXYGEN** |  |  |  |  |  |  |  |  |  |  |  |  |  |  |  |  |  |  |  |  |
| **INTUBATION** |  |  |  |  |  |  |  |  |  |  |  |  |  |  |  |  |  |  |  |  |
| **VENTILATOR** |  |  |  |  |  |  |  |  |  |  |  |  |  |  |  |  |  |  |  |  |
| **ICU** |  |  |  |  |  |  |  |  |  |  |  |  |  |  |  |  |  |  |  |  |
| **STEROID** |  |  |  |  |  |  |  |  |  |  |  |  |  |  |  |  |  |  |  |  |
| **ARF** |  |  |  |  |  |  |  |  |  |  |  |  |  |  |  |  |  |  |  |  |
| **ARDS** |  |  |  |  |  |  |  |  |  |  |  |  |  |  |  |  |  |  |  |  |
| **SHOCK** |  |  |  |  |  |  |  |  |  |  |  |  |  |  |  |  |  |  |  |  |
| **SEPTICEMIA** |  |  |  |  |  |  |  |  |  |  |  |  |  |  |  |  |  |  |  |  |
|  |  |  |  |  |  |  |  |  |  |  |  |  |  |  |  |  |  |  |  |  |

**REMARKS____________________________________________________________________________________________________________________**

## Appendix K: Study Completion and Outcome Report

**AYUSH COVID-19 PATIENT PROTOCOL 2020**

**STUDY COMPLETION AND OUTCOME REPORT**

Id:______________

PATIENT NO: ________________ PATIENT INITIALS:______________________ DATE:____________________

VITAL SIGNS:

Temp: ________ Pulse rate: _______Respiratory Rate : _______Blood Pressure: ________mm Hg

Physical Examination (Please tick):

|  | Normal | Abnormal | If Abnormal, please comment |
| --- | --- | --- | --- |
| General Appearance | **□** | **□** |  |
| Skin | **□** | **□** |  |
| Head, Neck & Thyroid | **□** | **□** |  |
| Eyes | **□** | **□** |  |
| Nose and Throat | **□** | **□** |  |
| Lymph Nodes | **□** | **□** |  |
| Cardiovascular | **□** | **□** |  |
| Lungs | **□** | **□** |  |
| Abdomen | **□** | **□** |  |
| Central Nervous System | **□** | **□** |  |
| Others – Specify | **□** | **□** |  |
|  | **□** | **□** |  |

Patient Patient’s Global Assessment of Tolerability to Therapy (4 grades):

□ Excellent tolerability

□ Good Tolerability

□ Average tolerability

□ Poor tolerability

**PROBABLE OUTCOMES:**

□ Infection free

COVID-19 TEST:□NEGATIVE □POSITIVE

CHANGE IN DISEASE STATE: □MILD TO MODERATE; □MODERATE TO SEVERE

BODY TEMPERATURE: NORMAL □YES □NO

COUGH :□MILD □ ABSENT

BREATHLESSNESS: □MILD □ABSENT

SpO2 NORMAL □YES □NO

SHIFTED TO ICU: □YES □NO

□Withdrawal (Non- COVID 19 related)

□DEATH

□Others _____________________________________________________________________

Observation ends 12 weeks after the start of investigational product **□ Yes □ No**

If ‘No’ indicate the Date /Visit No. of early cessation of the study :___________________

**Therapy Interruptions:**

Therapy with the investigational drug may be interrupted when adverse events occur.

□ Yes □ No

If answered ‘Yes’ please give duration of therapy interruptions.

Therapy Interruptions:

From : __________________ to _____________________

From : __________________ to _____________________

**Reason for early cessation of study :**

Therapy is to be discontinued : [ Please tick √ as appropriate]

□ Therapy refusal/ if a patient withdraws his/her consent.

□ If treatment fails to achieve the desired effect and the investigator considers another therapy to be more effective for medical reasons

□ Significant protocol deviation *

□ Serious adverse event

□ Significant Laboratory abnormality in the opinion of the investigator

□Loss to follow-up

□ Poor compliance*

□ Pregnancy

□ Intercurrent medical problem*

□ Death

* Please clarify in remarks

#### In the event of study discontinuation Comments

(Please specify in detail under remark)

_____________________________________________________________________________

Date of the latest treatment under the study _____________________

Date and time of the latest contact between

Investigator and patient ______________________

________________________________________________________________________________

Remarks of the Investigator: ________________________________________________________________________________

Signature of investigator with date : __________________________________________________

## Appendix N: Self-Reported Questionnaire

**AYUSH COVID-19 PATIENT PROTOCOL 2020**

**SELF REPORTED QUESTIONNAIRE**

PATIENT NO: ________________PATIENT INITIALS :_____________DATE:____________________

1. Do you feel Feverish? □ Yes □ No
2. Do You have sore throat □Yes □No
3. Do you have Nasal stuffiness/Sneezing/Runny Nose? □Yes □No
4. Do You have Cough □Yes □No
5. Did you Suffer from any symptom that could be due to the study drug □Yes □No

If Yes, ____________________________________________________________________

________________________________________________________________________

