# CLINICAL EVALUATION INCLUDING AYURVEDIC ASSESSMENT

Both Allopathic and Ayurvedic physicians, and predesignated study personnel will carry out assessment of all study patients as per the study schedule of events and timelines shown in Fig 1. and in Appendix A.

Several of the patient centric assessments including health and quality of life measures will be completed by the study paramedic without the knowledge of the drug allocation of the patient (assessor blind).

Standard study case record forms will be used on patient enrolment (baseline) to record patient data and will included demographics, personal habits, comprehensive medical history and examinations, measures of health and quality of life (Appendix H). The Ayurveda physician will also record the required clinical parameters of the study patient in the Ayurveda Case Record Form (Appendix I).

The routine hospital case record sheet will be used to record the patient’s progress while in hospital. The study investigator and the Ayurvedic physician will extract the relevant data of the patient from the hospital case sheet on a daily basis and enter it into the ‘study progress sheet’. (Appendix J).

On completion of treatment and at time of discharge, the investigators will complete the study completion case record form which will also include parameters on outcome (recovery or death) (Appendix K). The study patients will be provided with a precise follow-up schedule for the post treatment evaluation and during which the patients will be assessed as per schedule of events (Table 1) at weeks 4, 8 and 12 (study completion). It should be noted that some patients may require a longer period to recover that may extend from 3-4 weeks and in which case the assessment at discharge will also comply with the requirements of week-4 time endpoint (see Table 1).

During the study period, the study patient will complete a self-reported questionnaire on COVID 19 related symptoms daily which will be provided in the form of a mobile application. The self-reported questionnaire is enclosed in Appendix L.

All patients withdrawn for any reason will complete a medical examination and complete other documents as required on study completion (see above). If possible, laboratory evaluation as described above for study completion will also be done.

Laboratory and imaging investigations will be carried out as per Table 1 and are further described below.

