**19.3. Mobile phone Application**

A special software program as mobile application (AYUSH COV-2 CT App) will be downloaded by the study participant under supervision of the study investigator at the time of enrollment. The App will have a 2-way communication between participant and local investigator-through SMS and phone call. It will also record DAILY the response of the participant to 5 cardinal questions regarding presence and absence of =Fever, Sore throat, Cough, Breathlessness and Suspected Drug Side Effect. In addition, there will be a 6^th^ question- ‘do you wish to speak to investigator’. The participant will complete the response every day between 8-10 pm. The App will send the response daily to the study computer of the local investigator and central monitoring cell (CMC). In case, the study patient fails to complete the response in time, the App will raise a frequent alarm bell pop up response on the mobile phone of the study participant. In case, the response is YES to any of the questions, there will be an alarm bell type visual and audible response raised both the desktop computer and mobile phone of the local investigator and person in charge CMC. This will ensure speedy necessary action by the local site investigator. The App will stay active throughout the study duration.

**19.4 Ethics Committee Approval**: A copy of the formal written notification approving the study will be obtained from the EC duly signed by the chairman or any person so authorized, prior to commencement.

**19.5 Case Record Forms**: All complete CRFs duly signed by the investigator and counter signed by principal investigator must be submitted within one month of the completion of the study to the Principal Investigator.

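### Section 19.3 and the appended daily questionnaire give the app different question lists; if the app is built from the form, isolated new breathlessness at home would trigger no automatic alarm

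*Combined protocol and SAP*

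**What the plan says.** Three places in the protocol describe the same daily instrument.

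- **Clinical Evaluation Including Ayurvedic Assessment.** It states that "the study patient will complete a self-reported questionnaire on COVID 19 related symptoms daily which will be provided in the form of a mobile application", and says that the questionnaire is enclosed as Appendix L.
- **Section 19.3, Mobile phone Application.** The app records daily answers to "5 cardinal questions regarding presence and absence of =Fever, Sore throat, Cough, Breathlessness and Suspected Drug Side Effect". A sixth question follows: "do you wish to speak to investigator". The alarm rule is given here and nowhere else: "In case, the response is YES to any of the questions, there will be an alarm bell type visual and audible response", which reaches the local investigator and the central monitoring cell. On duration, "The App will stay active throughout the study duration".
- **The Self-Reported Questionnaire.** It is headed Appendix N, not L, and has five items: feverishness, sore throat, a nasal item ("Do you have Nasal stuffiness/Sneezing/Runny Nose"), cough, and symptoms possibly due to the study drug. It has no breathlessness item and no request for contact.

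The visit lists in Section 15 label the questionnaire as the mobile app, so the form and the app are meant to be one instrument. The study flow diagram (Fig 1) places daily contact after discharge in a mobile phone application as well.

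**The concern.** An app developer or a site reading this protocol has two item lists, and no statement of which one governs. The item that differs matters. Breathlessness is part of the clinical recovery definition (Section 11.1), and absence of dyspnoea is one of the secondary timelines (Section 11.2). Respiratory distress is among the severe-disease criteria in Section 10, to which the safety stop rules in Section 14 refer. A question about nasal symptoms does not stand in for it.

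An alarm can respond only to questions that are asked. If the app carries the form's items, the automatic route by which a discharged patient could report new breathlessness is lost, and so is the item by which any patient could ask for a call.

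It is not safe to assume that the appendices were checked against the main text. Appendix O describes its tests as belonging to a prophylaxis protocol, and the adverse event form in Appendix Q names two drugs that are not this protocol's investigational products. That the symptom form was also carried over from elsewhere is an inference, but it is a reason not to presume that the app follows Section 19.3.

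**Working it through.** The plan gives no figure to reproduce here. The check is a comparison of items, followed by the consequence under the any-YES rule.

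**Step 1: the items.**

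| Question | Section 19.3 | Appended form |
|---|---|---|
| Fever | yes | yes |
| Sore throat | yes | yes |
| Cough | yes | yes |
| Breathlessness | yes | no |
| Suspected drug effect | yes | yes |
| Wish to speak to the investigator | yes | no |
| Nasal symptoms | no | yes |

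Four of the five cardinal questions match, or four of all six. Two are missing from the form and one is extra.

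**Step 2: the alarm under each list.**

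| Patient at home | App uses Section 19.3 | App uses the form |
|---|---|---|
| Breathlessness with fever, cough or sore throat | alarm | alarm |
| Breathlessness attributed to the drug | alarm | alarm |
| Breathlessness alone, not attributed to the drug | alarm | none |
| No listed symptom, but wants to speak to the investigator | alarm | none |
| Nasal symptoms alone | none | alarm |

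There is one further case. The recovery definition in Section 11.1 tolerates mild cough, mild sore throat or nasal congestion. A recovered patient may therefore already be answering YES each day. On the form, adding breathlessness would leave that patient's answers unchanged. The alarm would sound, but it would carry no new information.

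**Step 3: time over which this applies.** The study lasts 12 weeks, that is 12 × 7 = 84 days, counted from admission (Section 5). Section 8 expects most discharges 5 to 15 days into hospitalization.

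- Days at home: 84 − 15 = 69 to 84 − 5 = 79.

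**Step 4: effect on the onset date of dyspnoea.** If the app does not ask, the next scheduled record is a study visit. Appendix A merges the week 4 visit into discharge when the two fall within 2 weeks of each other.

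- Discharge on day 5 to 13: next visit at week 4, a gap of 28 − 13 = 15 to 28 − 5 = 23 days.
- Discharge on day 14 or 15: week 4 is merged, so the next visit is week 8, a gap of 56 − 15 = 41 to 56 − 14 = 42 days.
- Later gaps: 28 days.

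These gaps ignore the 3 to 5 day visit window (Section 19.10) and any unscheduled contact. They bound the loss of precision in the date; they do not imply that the event goes unrecorded.

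**The case against.** Much of the opposing case is sound, and it limits the point.

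**A reader might infer that a patient worsening at home raises no alert.** The documents do not support that. The alarm is defined only in Section 19.3, whose list includes breathlessness, and no text says that the app was built from the form. Even on the form's list, a YES to fever, sore throat, cough, nasal symptoms or a suspected drug effect sounds the alarm. The silent case is narrow: new breathlessness, or another unlisted symptom, with NO to all five items.

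**There are other routes.** The app allows two-way SMS and calls, the patient card (Appendix S) has a 24-hour number, and Fig 1 provides for daily contact after discharge about any symptom. This stands in part. The Fig 1 contact runs through the same app, so it is not shown to be independent. The patient diary (Section 14) is for suspected drug symptoms and is read monthly. An Appendix A footnote calls for daily pulse oximetry, but no home reporting route is described.

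**A reader might infer that dyspnoea, pneumonia and oxygen data would be missing.** They would not. Dyspnoea, respiratory rate, oxygen saturation, oxygen use and pneumonia are on the daily progress report (Appendix J). Breathlessness is on the Ayurveda follow-up form (Appendix I) and the completion report (Appendix K). Symptoms and oximetry are assessed at weeks 4, 8 and 12 (Section 15). What is lost is precision in dates between visits.

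**A reader might use Tables 1 and 2 as a rate of missed events at home.** They come from hospital cohorts and do not measure new dyspnoea after discharge. The timing also depends on the day of admission. Table 2 puts admission at about 7 to 9.1 days from onset; adding 5 to 15 days gives discharge on illness day 12 to 24.1 (7 + 5 and 9.1 + 15). That is after the dyspnoea medians of 5 to 8 days and at or after the ICU admission medians of 10.5 to 12 days, with overlap only in the upper tails. If admission were assumed on illness day 2, since early enrolment is encouraged, discharge would fall on day 7 to 17 and the overlap would be larger. Neither scenario yields a rate.

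**Conclusion.** The contradiction is established by direct comparison: the form that the app is said to deliver lacks two of the six questions in Section 19.3 and adds one that Section 19.3 does not have. The consequence is conditional. If the app is built from the form, a discharged patient with breathlessness as the only new symptom, not attributed to the drug, triggers no automatic alarm. The contact request also disappears, and the date of new dyspnoea between visits becomes less precise, with scheduled assessments 15 to 42 days apart. If the app is built from Section 19.3, none of this follows, but the appended form is then wrong.

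The exposure is 69 to 79 days at home per patient, assuming that the 84 days run from admission and that discharge falls in the range the protocol expects. How many patients would have isolated breathlessness in that time cannot be derived from the documents. The point rests on the conflict in a safety instrument, not on an event count, and it should be settled before the form or the app is used.

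**What to change.** Reconcile the clinical evaluation section, Section 19.3 and the appended questionnaire to one stated item list for the app.

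- Bring the form into line with Section 19.3 by adding a yes/no item on breathlessness and a yes/no item on wishing to speak to the investigator, both under the existing any-YES alarm.
- State whether the nasal item stays and, if so, whether a YES to it triggers the alarm.
- Correct the appendix letter. The text cites L; the form and the contents list use N, which is also the letter of the health-related behaviour questionnaire.

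The cost is two yes/no questions on a one-page form and in the app, both already called for in Section 19.3, and a corrected cross-reference. No visits, staff or analyses are added.

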**17.2 Statistical Analysis:**

Whenever suitable, both completer and an intent-to-treat analysis with ‘last observation carried forward’ will be performed; for intent-to-treat analysis the patient should have completed at least 4 weeks of intervention and completed the follow up visit at 4 weeks post enrollment.

All statistical processing will be performed using SPSS & BMDP software unless otherwise stated.

The data will be individually analyzed for central tendencies (mean, median), range, standard error, standard deviation and 95% confidence intervals for each intervention arm in each of the groups in the study. Data will be tabulated and graphically shown using standard format and MS Excel and other software programs. Though ANOVA will be used for most of the measures, standard parametric (Student t-test) and non-parametric statistical tests (Mann Whitney statistic, Kruskal Wallis test) will be used depending upon the normality of the data. Fisher’s exact test or Chi Square will be used to test the proportion of patients classified as efficacy failures and those with AE (calculate exact binomial 95% Confidence Interval).

The primary efficacy measures of ‘mean time to clinical recovery’ and ‘proportion of patients with clinical recovery’ in the two arms will be compared using appropriate statistical tests; ANOVA for ‘mean time’ and two proportion z-test for proportion of patients.

Secondary efficacy measures in the two arms will also be compared and Bonferroni correction will be applied for multiple comparisons.

Risk ascertainment will be done for selected variables. Regression analysis (multivariate and step down) will be used to identify predictors for important outcomes. Survival analysis will be carried out to compare the two interventions (HCQ and Ashwagandha) for primary efficacy at different study time points.

Within arm efficacy will be evaluated by a one sample Student t-test.

Significance for each statistical test result will be considered at two-sided p< 0.05.

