## Appendix P: Classification of Adverse Events

**CLASSIFICATION OF ADVERSE EVENTS**

Adverse Events (AE):

All observed or volunteered adverse events regardless of treatment group or suspected causal relationship to study drug will be recorded on the AE Form. All AE’s must be classified according to their severity as Mild, Moderate and Severe.

For all AE, the investigator must pursue and obtain information adequate both to determine the outcome of the adverse event and to assess whether it meets the criteria for classification as a Serious AE.

Follow-up of the adverse event even after the date of therapy discontinuation, is required if the AE or its sequelae persist. Follow-up is required until the event or its sequelae resolve or stabilize at a level acceptable to the Investigator.

*Please note that AE are not limited only to adverse drug reactions. Any noxious event and or a medically important deviations from normality will be recorded as AE.*

Criteria for determining category of relationship of AE to trial treatment will be as follows:

1. Not related: AE’s which are definitely attributed to other causes.

2. Unlikely: (must satisfy at least two)

- It does not follow a reasonable temporal sequence from administration of the test drug
- It could readily have been produced by the patients clinical state, environmental or toxic factors, or other modes of therapy administered to the patient
- It does not follow a known pattern of response to the test drug
- It does not reappear or worsen when the drug is re-administered

3. Possible: (must satisfy at least two criteria) An AE may be considered possibly related if or when

- It follows a temporal sequence from administration of the drug
- It could not readily have been produced by the patient’s clinical state, environmental or toxic factors.
- It follows a known pattern of response to the test drug

4. Probable: (must satisfy three of the following)

- It follows a reasonable temporal sequence from administration of the drug
- It could not be reasonably explained by the known characteristics of the patient’s clinical state, environmental or toxic factors, or other modes of therapy administered to the patient
- It decreases or disappears on cessation or reduction in dose.
- It follows a known pattern of response to the test drug

5. Definitely (must satisfy all four criteria)

- It follows a reasonable temporal sequence from administration of the drug

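### Between visits, patients are prompted for adverse events only as suspected drug effects, which risks lower capture of minor events in the standard-of-care arm

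*Combined protocol and SAP*

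**What the plan says.** **Prompts put to the patient between visits**

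- The Self-Reported Questionnaire (headed Appendix N, cited in the text as Appendix L) has four items on COVID-type symptoms. Item 5 is its only adverse-event item: "Did you Suffer from any symptom that could be due to the study drug".
- Section 19.3 lists the five daily app questions as "Fever, Sore throat, Cough, Breathlessness and Suspected Drug Side Effect". A sixth asks "do you wish to speak to investigator". A Yes to any question raises an alert at the site and the central monitoring cell. The app runs for the whole study: "The App will stay active throughout the study duration".
- The section on clinical evaluation describes the form's purpose as COVID symptoms: "the study patient will complete a self-reported questionnaire on COVID 19 related symptoms daily".
- Section 14 asks patients to note in a diary any symptom they believe a drug has caused. The study physician reviews the diary at the monthly visits.

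**Recording and analysis rules**

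- Appendix P: "All observed or volunteered adverse events regardless of treatment group or suspected causal relationship to study drug will be recorded" on the AE form. Section 18.3 likewise requires every adverse event to be recorded whatever its cause.
- Section 17.2: "Fisher’s exact test or Chi Square will be used to test the proportion of patients classified as efficacy failures and those with AE", two-sided at 0.05.
- Section 5: open label, with SOC alone as the comparator. Section 4 places safety in the primary objective.

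**The concern.** The recording rule ignores cause, but each adverse-event prompt put to the patient between visits asks for a judgement about cause first. A patient on the Ayurveda drug takes it for 12 weeks and has an obvious candidate for any new headache or loose stool. A control patient knows that no study drug was added. After recovery, that patient receives only what the treating physician chooses, which may be little. The same minor symptom is therefore more likely to be reported in one arm than in the other.

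Two features could widen the gap. A Yes in the app triggers investigator contact, which can elicit further events. The diary also feeds the monthly review, so the attribution filter reaches part of the visit-based assessment.

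What is at stake is the between-arm AE comparison. With equal true rates, lower capture in the SOC arm would look like harm from the add-on drug, and no analysis can recover events that were never elicited.

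**Working it through.** **1. Time exposed.** Section 8 expects most discharges at 5 to 15 days, and the study lasts 12 × 7 = 84 days. Days after discharge: 84 − 15 = 69 and 84 − 5 = 79, or 69/84 = 82% to 79/84 = 94% of calendar time. This is a share of time, not of adverse events. Scheduled AE visits in that period are weeks 4, 8 and 12: three visits. They fall to two if discharge is within two weeks of week 4, because Appendix A then merges the week 4 assessment with discharge.

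**2. What the plan gives.** There are 70 patients per arm, by convenience (Section 17.1). No AE rate, capture rate or power is stated, so there is no figure of the plan's own to reproduce. Everything in steps 3 to 5 is assumption.

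**3. Effect of unequal capture.** Let both arms have the same true AE proportion, and let *r* be capture in SOC divided by capture in the Ayurveda arm. For illustration, 30% of patients have a minor post-discharge AE and 80% of these are recorded in the Ayurveda arm: 0.30 × 0.80 = 24%. The recorded SOC proportion is 24% × *r*. The table gives the probability that Fisher's exact test (two-sided 0.05, 70 per arm) declares a difference, by exact enumeration of two binomials.

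| *r* | Recorded, Ayurveda vs SOC | Probability of a false difference |
|---|---|---|
| 1 | 24% vs 24% | 0.03 |
| 0.9 | 24% vs 21.6% | 0.04 |
| 0.75 | 24% vs 18% | 0.10 |
| 0.5 | 24% vs 12% | 0.38 |
| 0.25 | 24% vs 6% | 0.82 |

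**4. What determines *r*.** Suppose visits capture a fraction *v* of AEs in both arms, and the between-visit prompts add 60% of the missed ones in the Ayurveda arm and a fraction *d* of them in SOC. Then *r* = [*v* + (1 − *v*)*d*] / [*v* + (1 − *v*) × 0.6].

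| Visit capture *v* | *r* if *d* = 0 | *r* if *d* = 0.3 |
|---|---|---|
| 0 | 0 | 0.50 |
| 0.5 | 0.5/0.8 = 0.63 | 0.65/0.8 = 0.81 |
| 0.8 | 0.8/0.92 = 0.87 | 0.86/0.92 = 0.93 |
| 0.95 | 0.95/0.98 = 0.97 | 0.965/0.98 = 0.98 |

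**5. Dilution by in-hospital events.** Section 17.2 does not restrict the AE proportion to the period after discharge. If 30% of each arm also has an independent, equally captured in-hospital AE, the Ayurveda proportion is 1 − 0.70 × 0.76 = 47%. The SOC proportion is 1 − 0.70 × 0.88 = 38% at *r* = 0.5 and 1 − 0.70 × 0.94 = 34% at *r* = 0.25. The probability of a false difference falls from 0.38 to 0.13 and from 0.82 to 0.27.

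**The case against.** The case against rests on the other routes, which apply to both arms.

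- Section 15 schedules AE monitoring at weeks 4, 8 and 12. The Appendix A footnote has a physician monitor AEs daily and gives no end date.
- The follow-up form in Appendix I is a long symptom checklist that does not ask about cause. It includes nausea, diarrhoea, rash and insomnia, just the minor events at issue.
- The Fig 1 notes describe daily contact after discharge for symptoms and complications in general, and the sixth app question is neutral.
- Serious events must be reported whatever the arm (Appendix P).
- The app item refers to a suspected drug effect, not to the study drug, so a control patient can report a side effect of an SOC medicine.
- The trial is exploratory, and the likely error would make the add-on look less safe rather than hide harm.

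Most of this stands. It rules out two readings that a reader might infer from item 5: that the daily item carries AE ascertainment after discharge, and that control patients must answer No to it.

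It does not remove the asymmetry. The daily contact in Fig 1 uses the app, and the app's listed questions include no general symptom item. The sixth question depends on the patient's initiative. The app wording is wider than item 5 but still asks for attribution to a drug. The checklist is scheduled for only two or three visits after discharge.

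**Conclusion.** The point holds as a risk of unequal ascertainment, confined mainly to minor, self-reported events between visits. The wording of the prompts is at odds with the plan's own any-cause, both-arm rule, and the likely direction is fewer recorded events in the SOC arm.

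The size cannot be derived from the documents. Under the assumptions above (equal true rates, 24% recorded in the Ayurveda arm, 70 per arm) it runs from negligible, 0.04 at a capture ratio of 0.9, to large, 0.38 at 0.5 and 0.82 at 0.25. Equally captured in-hospital events would reduce these figures. If visits catch most events, the ratio is near the benign end.

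It would be tempting to conclude that adverse events are under-counted in the SOC arm and that the comparison is biased. The documents do not establish that, because they say nothing about how much the visits and the checklist capture. The change is still worth making, since it is cheap before recruitment and the loss cannot be repaired afterwards.

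**What to change.** Use one neutral prompt, worded identically for both arms, in the questionnaire, the app and the diary. For example: *Have you had any new or worsened symptom or health problem since your last report, whatever the cause?* Add free text. The investigator then assigns relatedness under the Appendix P categories.

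At the same time, reconcile the two item lists: the questionnaire asks about nasal symptoms where Section 19.3 lists breathlessness. State which list is used.

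The cost is a rewording of three instruments and somewhat more app alerts to triage. With a capture ratio of 1, the false-positive rate of Fisher's test in the illustration returns to 0.03. Nothing in dosing, visit schedule or sample size changes.
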